Our team has developed a balance training platform that integrates visual feedback balance training (VFBT) with closed-loop FES for ankle muscles [24,37,38]. We have tested the feasibility and preliminary efficacy of this protocol in individuals with incomplete SCI who had difficulty in balance but were still able to stand without support [24,39]. However, for individuals with lower levels of function, particularly those with knee and hip impairments, FES for the ankle muscles may be insufficient to provide the postural support necessary for effective balance training [27,40,41]. Although proximal muscles could be stimulated by additional FES channels, this would significantly increase the system’s complexity. Rather, TSS offers a more effective way to concurrently modulate excitability across several spinal segments [28–30,36], and to augment multi-muscle activation without adding technical burden. This synergistic interaction is supported by preliminary results from our research group in people with incomplete SCI, showing greater functional benefits when TSS is administered concurrently with closed-loop FES (TSS + FES) during balance tasks [42,43].

Given the novelty of this combined neuromodulation approach and the lack of feasibility data in PwMS, a pilot randomized controlled trial (RCT) is warranted before designing a fully powered RCT. Therefore, the main purpose of this study is to assess the feasibility, acceptability, safety, and adherence of neuromodulation-augmented balance training interventions in PwMS. The second purpose is to investigate the preliminary clinical efficacy on balance performance, mobility, balance confidence, fear of falling and neural excitability. We hypothesize that the intervention will be feasible and acceptable with minimal adverse events, and that the combined neuromodulation group (TSS + FES) will show greater functional and neurophysiological improvements than FES-only or sham stimulation groups.

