## 2. Methods & materials

### 2.1. Participants & eligibility criteria

This multi-method study includes a pilot RCT to evaluate feasibility, acceptability, safety and preliminary efficacy of this novel neuromodulation-augmented balance training program and a qualitative descriptive study to capture patients’ experiences and perspectives [44]. This study will take place at the Lyndhurst Centre, a tertiary rehabilitation hospital, and has been approved by the University Health Network Research Ethics Board (Approval #25–5549, Version 5, December 29, 2025) and is registered at ClinicalTrials.gov (Identifier: NCT07174973). A formal sample size calculation is not required, as this is a pilot RCT [45]. We plan to recruit 24 participants (eight in each group), based on our previous studies in people with SCI using non-invasive neuromodulation.

For recruitment, we will use multiple strategies, including clinicians’ referrals, posting flyers at outpatient MS clinics, community MS programs, and existing research registries/databases (MS Canada). Participants will be allowed to continue their usual medical care throughout the study period. Written informed consent will be obtained from all eligible participants prior to baseline assessment. Given the small sample size, single-site design, and low-risk nature of the interventions, a formal independent data monitoring committee will not be required for this pilot RCT. Participant safety and study conduct will be monitored by the principal investigator, and any adverse events will be reported to the University Health Network Research Ethics Board. In addition, ongoing monitoring will occur through regular research team meetings to review recruitment progress, protocol adherence, intervention fidelity, data completeness, and adverse events.

Fig 1 shows the SPIRIT Timeline for the study, Table 1 summarizes the inclusion and exclusion criteria, and Table 2 shows the template for Intervention Description and Replication (TIDieR) checklist.

**Table 1 pone.0346491.t001:** Inclusion and exclusion criteria.

Criteria	
Inclusion	Confirmed diagnosis of MS based on the revised McDonald criteria Age 18–65 years Ability to walk at least 100 meters with or without an assistive device Self-reported balance difficulties during daily activities

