### 2.2. Randomization, allocation, and blinding

Participants will be randomly assigned into three groups following baseline assessment using a computer-generated covariate-adaptive algorithm, including two variables: (1) gender, and (2) baseline postural control using the forward reach test of the Berg Balance Scale (BBS). To ensure balanced allocation of people with different levels of function, participants with scores of 0–2 in the forward reach test (i.e., reaching forward ≤2 inches) will be categorized as having low postural control, while those with scores of 3–4 (i.e., reaching forward ≥5 inches) will be categorized as having high postural control. Outcome assessors conducting clinical assessment will be blinded to group assignment. The neurophysiological assessments will be conducted by one of the therapists delivering the intervention and will therefore not be blinded. Since the neurophysiological assessment involves standardized instrumentation, they are less susceptible to assessor bias [46]. Participants will remain blinded through the use of sham stimulation.

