### 2.5. Assessment timeline

As outlined in Table 1, feasibility and safety outcomes will be measured throughout the study. Acceptability outcomes will be measured post-training immediately. Clinical outcomes will be measured at three time points: (1) baseline, (2) immediately post-training (two or three days after completing the 12 sessions), and (3) eight-week post-training. There will be two visits at each time point: one for clinical and mobility assessments, and the other for neurophysiological testing and an interview. Safety outcomes will be measured throughout the study.

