### 2.6. Data management & analysis

Study data will be entered into a secure, password-protected electronic database by the University Health Network. Participants will be assigned a unique study identification number, and identifying information will be stored separately from research data. Electronic data will be stored on the secure institutional server, and paper records will be stored in locked cabinets in the secured research office. Feasibility outcomes (recruitment, retention, adherence, completion rates) will be summarized descriptively using means, standard deviations, frequencies, and percentages. Regarding TAM-2, items will be grouped into predetermined domains, and scores within each domain will be averaged to generate domain-specific scores. Conventional content analysis will be used to analyze the interview transcripts, given the exploratory nature of the study and limited research in this area. Interviews will be recorded, transcribed, and analyzed inductively by two members of the research team. The researchers will independently review the same transcripts, then meet to identify codes and create a preliminary codebook. This process will be repeated until a final codebook is created, and then the final codebook will be applied to the transcripts. Next, the research team will meet to review the codebook and group the codes, which will then be organized into categories and themes [24,39,61]. Adverse events will be reported descriptively by frequency and type.

All statistical analyses will be performed using SPSS (IBM SPSS, Chicago, USA) for the available data. A two-way repeated-measures ANOVA (group × time) will be conducted to analyze changes in clinical and neurophysiological outcomes across three study groups and time. The effect sizes with 95% confidence intervals will be reported, and the proportion of missing data (if applicable) will be described to inform the design and sample size calculation of a future fully powered trial.

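### The stated group × time ANOVA treats baseline as a time level and omits both allocation covariates, which costs modest precision for outcomes with low to moderate baseline-to-follow-up correlation

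*Protocol article*

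**What the plan says.** Section 2.2 allocates participants "using a computer-generated covariate-adaptive algorithm, including two variables: (1) gender, and (2) baseline postural control", the latter being the forward-reach item of the Berg Balance Scale (BBS) split into low (0–2) and high (3–4).

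Section 2.5 sets the schedule: "Clinical outcomes will be measured at three time points: (1) baseline, (2) immediately post-training", with the third assessment eight weeks after training.

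Section 2.6 then states the model: "A two-way repeated-measures ANOVA (group × time) will be conducted to analyze changes in clinical and neurophysiological outcomes across three study groups and time". It names no covariate. It adds: "The effect sizes with 95% confidence intervals will be reported", to inform the design and sample size of a full trial. The Discussion likewise says the clinical results will supply the effect size and variance for that trial.

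The Introduction hypothesises that "the combined neuromodulation group (TSS + FES) will show greater functional and neurophysiological improvements than FES-only or sham stimulation groups". Section 2.1 fixes the size: "We plan to recruit 24 participants (eight in each group), based on our previous studies in people with SCI using non-invasive neuromodulation". Section 2.4.4 labels efficacy exploratory.

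**The concern.** The trial balances its arms on two covariates and measures almost every efficacy outcome at baseline, but the stated model uses neither as an adjustment. With baseline as a level of the time factor, the group × time contrast between baseline and post-training is the difference between arms in mean change.

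Two things are at stake.

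- **Precision.** At 8 per arm it is scarce, and the intervals and variances are the outputs meant for the next trial. Change-score variance is 2(1−rho) in outcome-variance units, against 1−rho² after baseline adjustment. A full trial that will adjust for baseline but is planned on change-score variance would be made larger than it needs to be.
- **Chance imbalance.** Arms of 8 can differ appreciably at baseline, and a change-score contrast passes part of that difference into the estimated effect.

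**Working it through.** **Inputs from the article.** Three arms of 8 (3 × 8 = 24, the only design figure stated), three time points, 95% intervals, two binary allocation factors. No SD, correlation, power or interval width is given, so there is no precision figure to reproduce.

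**Assumptions.** Equal outcome SD at each time, two-sided t intervals, error pooled over the three arms, and rho from 0.3 to 0.95. Results are in outcome SD units.

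**Half-width of the 95% interval for one pairwise contrast at one follow-up time**

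- Planned, change contrast: t × √[2(1−rho) × 2/8]. Here t = 2.080 (21 df) for a single contrast, or 2.018 (42 df) with the pooled within-person error under sphericity.
- Adjusted for baseline: t × √[(1−rho²) × 2/8 × (1+1/19)], with t = 2.086 (20 df). The factor 1+1/19 is the average cost of estimating the baseline slope.
- Adjusted for baseline and both allocation factors, taking the factors as balanced across arms and uninformative: the same expression with t = 2.101 (18 df).

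Example at rho 0.5. Planned: 2.080 × √0.25 = 1.040. Baseline-adjusted: 2.086 × √(0.75 × 0.25 × 20/19) = 0.927. With factors: 2.101 × 0.444 = 0.933. Ratio 0.933/1.040 = 0.898, so 10% narrower.

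| rho | planned, 21 df | planned, 42 df | + baseline | + baseline and factors | last ÷ 21 df | last ÷ 42 df |
|---|---|---|---|---|---|---|
| 0.3 | 1.230 | 1.194 | 1.021 | 1.028 | 0.836 | 0.861 |
| 0.5 | 1.040 | 1.009 | 0.927 | 0.933 | 0.898 | 0.925 |
| 0.7 | 0.805 | 0.782 | 0.764 | 0.770 | 0.956 | 0.985 |
| 0.8 | 0.658 | 0.638 | 0.642 | 0.647 | 0.983 | 1.013 |
| 0.9 | 0.465 | 0.451 | 0.466 | 0.470 | 1.010 | 1.041 |
| 0.95 | 0.329 | 0.319 | 0.334 | 0.337 | 1.023 | 1.055 |

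In 4,000 simulated trials per setting with uninformative factors, the fully adjusted interval was narrower than the 21-df interval in 79% of trials at rho 0.5, 62% at 0.7, 52% at 0.8, 39% at 0.9 and 33% at 0.95.

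**Planning variance.** In a large trial the variance ratio, adjusted to change score, is (1−rho²)/[2(1−rho)] = (1+rho)/2: 0.75 at rho 0.5 and 0.85 at rho 0.7. It is below 1 for every rho under 1, because the small-sample costs disappear.

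**Chance imbalance.** For an outcome unrelated to the allocation factors, the SD of the baseline difference between two arms is √(2/8) = 0.5 outcome SD. Given a baseline difference d, the change contrast is shifted by −(1−rho)d. With d = 0.5 the shift is 0.25 SD at rho 0.5 and 0.15 SD at rho 0.7, against the direction of the imbalance. Baseline adjustment removes it in expectation.

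**Allocation factors.** An effect of gender or reach class that is the same at both times cancels in the change contrast. Simulated with minimisation (probability 0.85) and a reach-class effect of 0.8 residual SD at both times, mean full interval width went from 2.05 to 1.85 at rho 0.5, from 1.60 to 1.53 at 0.7 and from 0.92 to 0.94 at 0.9. Adding the two factors to a model that already had baseline changed almost nothing (1.857 to 1.851 at rho 0.5; 1.522 to 1.531 at 0.7). When the class effect acts on the follow-up value only, so that class predicts change, the widths went from 2.19 to 1.85 at rho 0.5 and from 1.71 to 1.53 at 0.7.

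**The case against.** The strongest reply has four parts.

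1. **The gain depends on an unknown rho.** This stands. At high rho, which is plausible for stable performance tests, the adjusted interval is no narrower and can be slightly wider. A reader might infer that every between-group interval in this trial is too wide. The documents do not support that: they give no correlation, and the table shows the sign changing.
2. **Omitting covariates used in allocation does not automatically inflate the standard error here.** This also stands. The usual argument concerns between-person comparisons with prognostic covariates. The change contrast already removes time-constant effects, and forward reach is itself a BBS item, so it overlaps with baseline BBS.
3. **The contrast is unbiased, and efficacy is exploratory.** Both are true. The shift from chance imbalance is conditional on the sample drawn and is not a bias of the design. The main purpose is feasibility, acceptability, safety and adherence, and no power claim is undermined. This limits the severity but does not remove the point.
4. **Covariates and pairwise contrasts belong in an analysis plan that is not shown.** This stands for the contrasts: naming an omnibus model does not exclude follow-up comparisons, so their absence is not a fault in itself. It does not stand for the model. The article states the model's factors and makes baseline a time point, so the choice is fixed in print and not merely left open.

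**Conclusion.** The point holds in a limited form. The stated model makes the post-training comparison one of change scores. Against the 21-df contrast, the fully adjusted interval is about 16%, 10% and 4% narrower at rho 0.3, 0.5 and 0.7. Against the pooled 42-df error the figures are about 14%, 7% and 2%. The gain is gone by about 0.8 (42 df) to 0.9 (21 df). Above that there is a loss of a few per cent.

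These figures rest on assumed values of rho, equal SDs over time, and allocation factors that are balanced and uninformative. If the factors predict change the gain is larger; if they do not, leaving them out costs nothing in this contrast. Protection against chance baseline imbalance is the other benefit. Severity is modest: an improvement to exploratory estimates, not a threat to the trial's validity.

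**What to change.** Replace the model sentence in Section 2.6 with wording such as: *For each outcome with a baseline value, the post-training and 8-week values will be modelled with group, time and group × time, adjusting for the baseline value of that outcome, gender and forward-reach class. Adjusted mean differences for TSS+FES minus FES, TSS+FES minus sham, and FES minus sham will be reported at each time with 95% confidence intervals. The global rating of change, which has no baseline value, will be adjusted for gender and forward-reach class only.*

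The pairwise differences are included because they are the comparisons the hypothesis names and the next trial needs.

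All covariates are already collected, so the change is one of wording. Its statistical cost is 3 of 21 residual degrees of freedom (t from 2.080 to 2.101, about 1%) plus the cost of estimating the baseline slope (√(20/19) = 1.026, about 3% on the standard error), and somewhat more if the allocation factors end up unbalanced. For very highly correlated outcomes the intervals will therefore be slightly wider than under the present plan.

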### 2.7. Knowledge translation plan

Findings from this study will be widely disseminated to relevant knowledge users, including PwMS and their caregivers, rehabilitation clinicians, rehabilitation researchers, and organizations engaged in MS care, through peer-reviewed publications, relevant conferences, and workshops. We anticipate that the findings will be disseminated across two to three publications: one publication will focus on feasibility outcomes, the second publication will report preliminary clinical and neurophysiological outcomes, and the third publication will focus on the qualitative findings to provide more details regarding the participant experiences, perceived barriers, and facilitators of the intervention, and suggestions for intervention refinement.

## 3. Discussion

Non-invasive neuromodulation techniques, including FES and TSS, have shown efficacy in improving walking and upper limb motor functions when coupled with active task-specific training in people with neurological conditions [23,29,30,33,62–65]. However, their potential effects as complementary interventions to improve balance in PwMS have yet to be investigated. This pilot RCT aims to fill this gap by assessing the feasibility of integrating technology specifically non-invasive neuromodulation and task-specific balance training via VFBT and evaluating its effects on balance, mobility, and neuroplasticity in PwMS. Running this pilot study will help to identify methodological, logistical, and implementation-related challenges prior to conducting larger RCTs [66–69].

In addition to feasibility and acceptability outcomes, the study includes a battery of clinical and neurophysiological assessments. These exploratory measures will help to determine whether neuromodulation-augmented VFBT has the potential to improve balance, mobility, balance confidence, and fear of falling. Neurophysiological assessment will help to provide preliminary insight into whether changes in corticospinal and spinal excitability are associated with functional improvements. These mechanistic measures are recommended in neuromodulation trials to identify the underlying neural mechanisms associated with recovery and guide the design of future studies [28,60].

The methodological strengths of this study are consistent with high-quality trials. The randomized, sham-controlled, and assessor-blinded design reduces bias, and covariate-adaptive randomization helps to normalize baseline differences and reduce heterogeneity across groups [70–72]. Furthermore, incorporation of semi-structured interviews offers a more in-depth understanding of participants’ experiences and perspectives, which is of great importance when considering to integrate neuromodulation techniques into rehabilitation settings. Preliminary clinical outcomes will help to calculate the effect size and variance necessary to plan a definitive RCT.
